## Abstract

**Background:**

Maternal substance use disorder (SUD) represents a risk condition for quality of parenting and child development. The current literature highlights the need to identify interventions that effectively enhance the quality of parenting and to better understand which mechanisms are involved in the process of change. The present study protocol describes a randomized wait-list controlled trial that aims to examine (1) the efficacy of the Video-feedback Intervention to promote Positive Parenting and Sensitive Discipline (VIPP-SD) in improving the quality of parenting (i.e., sensitive parenting and sensitive discipline) in mothers with SUD, (2) whether the intervention affects parental cognitive mechanisms (i.e., attentional disengagement to infant negative emotions, inhibitory control confronted with children’s affective expression, and parental reflective functioning), and (3) whether changes in these processes act as mechanisms of change, mediating the effect of the VIPP-SD program on quality of parenting. Moreover, the study aims (4) to explore whether the VIPP-SD has an effect on parenting stress and (5) to compare mothers with SUD to low-risk mothers on the outcome measures.

**Methods:**

The study will involve 40 mothers with SUD and 20 low-risk mothers of children aged between 14 months and 6 years old. Mothers in the SUD group will be randomly divided into two groups, one receiving the intervention (SUD experimental group) and one undergoing treatment as usual (SUD control group). All the mothers will be assessed pre-test and post-test. Quality of parenting will be assessed through observed parenting behaviors, whereas parental cognitive mechanisms will be assessed through neuropsychological tasks and self-report measures.

**Discussion:**

The results of the study will reveal whether an intervention that has been proven effective in other at-risk samples is also effective in improving parenting behaviors in the context of SUD. The results will also provide insight into potential cognitive mechanisms involved in the process of change.

**Trial registration:**

ISRCTN registry ISRCTN63070968. Registered on 25 June 2021. Retrospectively registered

**Supplementary Information:**

The online version contains supplementary material available at 10.1186/s13063-022-06420-8.

## Background

Quality of parenting plays a fundamental role in infant development [1] and is likely to be severely compromised in the context of maternal substance use disorder (SUD [2];), a clinical condition highly associated with dysfunctional parenting practices that in their most severe forms could lead to child maltreatment [3]. Several authors point to the importance of implementing interventions that besides focusing on the condition of drug abuse or dependence per se also target parental functioning, given that recovery from the first is not necessarily associated to improvements in the latter [4–7]. Moreover, a wide array of studies show the relevance of SUD-related cognitive impairments, as for example deficits in attention, memory, decision-making, and problem solving [8–10], to better understand which mechanisms could mediate the effect of interventions [11, 12]. In this regard, much work has been done with respect to adults with SUD (e.g. [13]), but little is known about how such cognitive impairments relate to parenting and parenting interventions in adults with SUD [7].

The present study protocol describes a randomized wait-list controlled trial in which we aim to examine the efficacy of the Video-feedback Intervention to promote Positive Parenting and Sensitive Discipline (VIPP-SD [14];) in improving the quality of parenting in mothers with SUD. Secondly, the study aims to investigate whether the intervention affects parental cognitive mechanisms, improving attentional disengagement to infant negative emotions, inhibitory control in front of children’s affective expression, and maternal reflective functioning. Finally, the study aims to detect whether changes in parental cognitive mechanisms play a role in mediating the effect of the VIPP-SD program on the quality of parenting measured through observed parenting behaviors. To accomplish this, we will compare mothers with SUD receiving the intervention (SUD experimental group) to mothers with SUD undergoing treatment as usual (SUD control group). Secondly, we will compare mothers with SUD to low-risk mothers recruited from the general population, to see whether the intervention reduces expected differences between mothers with SUD and low-risk mothers. In the following paragraphs, rationale, objectives, hypotheses, and methods of the study are presented, followed by a discussion of the possible implications.

### Quality of parenting in mothers with SUD

#### Observed parenting behaviors

Observed parenting behaviors constitute a key access to the quality of parenting in infancy and childhood, providing a measure of the parent’s ability to take care of the child and of the child’s actual experience of care [15–19]. Maternal SUD jeopardizes the quality of parenting behaviors, affecting in multiple ways sensitive parenting [15, 17, 20] and parental sensitive discipline [21, 22], two facets of positive parenting associated to favorable developmental outcomes in children [23, 24]. Compared to low-risk populations, mothers with SUD show less optimal sensitivity and responsiveness to children’s emotional signals [25–29] and are more inclined to be hostile, directive, and interfering with their activities [30–34]. These negative parenting behaviors have been linked to unfavorable outcomes in offspring, as insecure and disorganized attachments [35], and a higher risk to be involved with child protective services [36]. Moreover, mothers with SUD are more inclined to adopt negative disciplinary strategies [37], ranging from the use of harsh discipline [38–40] to the adoption of laissez-faire, characterized by withdrawal and lack of limit-setting, and role reversal [41, 42]. These practices tend to be ineffective and are related to several undesired developmental outcomes in children, including internalizing and externalizing problems [43, 44]. Therefore, parenting behaviors constitute one of the main targets of parenting interventions in the condition of SUD [45, 46]. In the present study, we aim to test the efficacy of the VIPP-SD, a short-term evidence-based parenting intervention based on attachment theory [17, 47] and social learning theory [48, 49], in improving positive parenting strategies in a clinical population of SUD mothers with young children. We will measure sensitive parenting and sensitive discipline using observational scales (the Emotional Availability Scales [50] and a scale for harsh discipline [51]) under various structured conditions (free-play and two compliance tasks), comparing mothers with SUD receiving the intervention to mothers with SUD undergoing treatment as usual (TAU) and to low-risk mothers. According to previous studies, we expect that (1) the quality of observed parenting behaviors in SUD mothers is higher after the intervention compared to the randomized control group receiving TAU and (2) mothers with SUD will, at pretest, show poorer parenting behaviors compared to the low-risk group.

### Cognitive mechanisms involved in parenting

#### Attentional mechanisms: attentional bias to child negative emotions

Attentional processing of child stimuli provides one of the basic cognitive mechanisms for sensitive parenting. Human adults present a selective bias in the processing of infant faces, which is of potential evolutionary value [52, 53] since it facilitates a detailed screening of facial mimicry and increases the likelihood of appropriate responses [54]. It has been shown that mothers present a preferential attentional bias for child negative emotions, finding it more difficult to disengage their attention from visual stimuli displaying sadness or distress [55, 56]. This process is attenuated in the presence of psychopathology and high parenting stress [53, 57] and has proved to be sensitive to treatment [54]. We hypothesize this same attentional mechanism to be disrupted in mothers with SUD, given the high incidence of parenting stress [58], psychopathology [59, 60], and the overlap between brain reward regions associated to substances and to infant-related stimuli [61, 62]. This hypothesis is further supported by studies that provide evidence for disruptions in normative attentional processes in the context of substance dependence [63, 64].

In the current study, we aim to test whether attentional bias to child face in mothers with SUD, measured with a computerized neuropsychological task, is enhanced through the application of the VIPP-SD. According to previous studies, we expect that (1) attentional bias to child negative emotions in mothers with SUD increases after the intervention compared to the randomized control group receiving TAU and (2) at pre-test, mothers with SUD will show lower attentional bias to child negative emotions compared to the low-risk group.

#### Inhibitory mechanisms: inhibitory control when exposed to child emotions

Inhibition of parenting negative strategies represents another basic cognitive mechanism of sensitive parenting [65]. At the cognitive level, the inhibition of non-optimal responses relies on inhibitory control, a “lower order” component of executive functions responsible for the regulation of attention, thoughts, or behaviors, according to internal and external stimuli [66–69]. Chronic drug use is associated with severe frontal and prefrontal cognitive dysfunctions which result in the inability to inhibit dominant behavioral responses activated by craving, which lead to the search and assumption of drugs [70–72]. Impairments in prefrontal activity are responsible for the onset and maintenance of substance dependence [70–75] and have been found in mothers with SUD also when observing infants displaying different emotional expressions [62, 76].

Traditionally, inhibitory control has been investigated through go/no-go paradigms, which involve the presentation of stimuli, alternating go conditions, where the individual has to respond to the displayed cue, and no-go conditions, where the individual has to inhibit their response [66, 77]. In the current study, we aim to test whether inhibitory control when exposed to child emotions in mothers with SUD, measured through a computerized emotional go/no-go task, improves after the administration of the VIPP-SD. We expect that (1) inhibitory control when exposed to child emotions in mothers with SUD will increase after the administration of the intervention compared to the randomized control group receiving TAU and (2) compared to the low-risk group, mothers with SUD at pre-test will show lower inhibitory control when exposed to child emotions.

#### Maternal reflective functioning

Reflective functioning describes the parents’ ability to reflect upon their own and their children’s experience and behaviors in terms of mental states [78–80]. This mechanism is associated with positive and negative parenting strategies [79, 81, 82] and with children’s use of their mothers as secure base [83]. Mothers with SUD present difficulties in emotion regulation [84] as well as poor reflective functioning abilities, with the risk to develop negative, idealized, or fragile representations of their children and their parental role [46, 85, 86]. Postnatal levels of mentalizing abilities have been identified as predictors of clinical prognosis in the context of substance abuse [87], and reflective functioning represents an important target of parenting interventions within this clinical population [46, 87]. Improvements in reflective functioning in response to parenting interventions have been associated with increases in quality of observed parenting behaviors and with improvements in children’s regulation [7, 85]. For the purposes of the present study, we will examine self-reported maternal reflective functioning pre- and post-intervention. We expect that (1) reflective functioning in mothers with SUD improves after the intervention compared to the randomized control group receiving TAU and (2) mothers with SUD at pre-test present lower reflective functioning abilities with respect to the low-risk group.

#### Other variables relevant in the context of maternal SUD

Given the complexity of the SUD condition, especially in mothers, various domains of adult functioning will be included as control variables in the present study. A brief description and rationale for each one is reported below.

##### Parenting stress

Mothers with SUD are more likely to experience high levels of stress in their caregiving role, much of which is dependent on the condition of substance addiction and related risk factors, such as health conditions and psychosocial difficulties [58, 62, 88, 89]. The reiteration of substance use in time decreases the salience of infant-related stimuli that become less rewarding for mothers and risk to be perceived as a source of additional stress rather than part of a mutually fulfilling system [62, 90]. High levels of parenting stress have been often linked with difficulties in providing high-quality parenting and are associated with hurdles in mother-child interactions, lack of parental warmth, and increases in harsh parenting [91]. For the purpose of this study, we will measure parental stress using the short form of the Parenting Stress Index [92] before and after the intervention, expecting a decrease in levels of stress after treatment.

##### Maternal psychopathology

Individuals with SUD present an increased risk for psychopathology and psychological maladjustment [93, 94], which has been linked to poor executive functioning [95] and to several adverse treatment outcomes, such as increased severity in individual maladjustment and early relapse to substance use [96]. The presence of psychopathological symptoms in mothers with SUD represents an additional risk factor for caregiving practices, exacerbating difficulties experienced during mother-child interactions and increasing the risk to adopt negative parenting strategies [97–99]. In the present study, we will control for the potential confounding role of maternal psychopathology when examining the efficacy of the VIPP-SD. Maternal psychopathological symptoms and psychological distress will be measured pre- and post-treatment and considered as a confounder.

##### General executive functioning

Inhibitory control represents a “lower order” component of executive functions and, together with working memory and cognitive flexibility [66, 100, 101], allows for the activity of “higher order” executive functions, such as reasoning, problem solving, and planning [66, 102, 103]. A wide array of research has highlighted that individuals with chronic and heavy substance abuse present with damages to executive functioning, which could act as predisposing, retention, and relapse factors for substance assumption [11–13, 104–106]. Moreover, research on parenting found some associations between executive functions and parental practices [68, 69]. In the present study, we will control for the potential confounding role of general executive functioning to investigate the specific impact of VIPP-SD on parental inhibitory control when exposed to child emotions and to ascertain its role as a mechanism of change in parenting behaviors. Mothers’ general executive functioning will be measured pre- and post-treatment and its residual score after taking into account its overlap with inhibitory control will be used as a potential confounder in statistical analyses.

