### Control variables

When testing changes in the mothers’ attentional disengagement, inhibitory control, and reflective functioning, we will control for the potential confounding roles of general maternal executive functions, and maternal psychopathology. As far as it concerns general executive functions, we will measure inhibitory control, working memory, cognitive flexibility, and planning through standardized neuropsychological tasks involving neutral stimuli. Specifically, we will use a go/no-go task [142], the Corsi Block-Tapping Task [143, 144], a short-form of the Berg Card Sorting Test [145–148], and the Tower of London Test [149–151]. All the tasks are computerized and retrieved from the open source software system PEBL - Psychology Experiment Building Language [152].

Concerning maternal psychopathology, we will administer the Symptom Checklist-90 Revised [153], a 90-item self-report questionnaire designed to evaluate the presence of psychopathology along different symptom dimensions and global distress indexes.

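### Adjustment for psychopathology and executive function is not limited to pre-test values, and the residualised executive-function score leaves some or all of the confounding of the inhibitory-control path in place

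*Protocol article*

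**What the plan says.** Four places in the protocol article bear on this.

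- *Maternal psychopathology* (Background): "we will control for the potential confounding role of maternal psychopathology when examining the efficacy of the VIPP-SD". It continues: "Maternal psychopathological symptoms and psychological distress will be measured pre- and post-treatment and considered as a confounder".
- *General executive functioning* (Background): this construct, too, is assessed at both time points. On the form in which it enters the models, the section states: "its residual score after taking into account its overlap with inhibitory control will be used as a potential confounder in statistical analyses". One stated purpose is to isolate the child-emotion inhibitory-control measure and "to ascertain its role as a mechanism of change in parenting behaviors".
- *Control variables* (Methods): when changes in attention, inhibitory control and reflective functioning are tested, "we will control for the potential confounding roles of general maternal executive functions, and maternal psychopathology". The executive-function battery listed there includes a go/no-go task with neutral stimuli.
- *Other variables relevant in the context of maternal SUD* (Background): "various domains of adult functioning will be included as control variables in the present study". Parenting stress is the first domain described under that heading.

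*Statistical analyses* specifies mixed and repeated-measures models with condition and time as factors, and a mediation analysis of changes. It names no covariates. Under *Randomization*, allocation is 1:1 and is disclosed only after the pre-test.

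**The concern.** Two rules are fixed in a way that can mislead.

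**Timing.** A variable measured after allocation cannot be a confounder of a randomised comparison. If treatment moves it, it is a consequence of treatment, and conditioning on it takes away part of the effect or opens a path through unmeasured common causes. The text calls the variables confounders directly after stating that they are measured at both times, and the models have time as a within-subject factor. An analyst following it literally could enter them as time-varying covariates.

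**Form.** The mediator is not randomised, so the path from inhibitory control to parenting can be confounded by general executive function. The shared part of executive function and inhibitory control is what carries that confounding, and residualising discards it. The mechanism result could then be reported as adjusted for executive function when little or no adjustment has taken place.

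**Working it through.** The protocol states no figure to reproduce here. The only document input is d = 0.47 from *Sample size and power*, used there for the primary, secondary and fourth aims. Every other coefficient below is an assumption.

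**1. Post-test covariate in the arm comparison**

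Let outcome and covariate have within-arm SD 1. Treatment lowers symptoms by g, and symptoms correlate −r with outcome within arm.

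Adjusted effect = outcome difference − slope × covariate difference = 0.47 − (−r)(−g) = 0.47 − r·g.

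| g | r | Adjusted effect |
|---|---|---|
| 0.2 | 0.3 | 0.47 − 0.06 = 0.41 |
| 0.3 | 0.5 | 0.47 − 0.15 = 0.32 |
| 0.5 | 0.5 | 0.47 − 0.25 = 0.22 |

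A simulation of 400,000 subjects, with a true total effect of 0.47, shows when the bias arises. Here a is the treatment effect on the covariate, b the covariate's effect on outcome, and u a shared unmeasured cause.

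| a | b = 0, u = 0 | b = 0, u = 0.5 | b = −0.3, u = 0 | b = −0.3, u = 0.5 |
|---|---|---|---|---|
| 0 | 0.467 | 0.470 | 0.476 | 0.465 |
| −0.2 | 0.470 | 0.421 | 0.408 | 0.357 |
| −0.4 | 0.470 | 0.371 | 0.349 | 0.249 |

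These are the post-test-adjusted estimates. Bias needs both a non-zero a and a relation between covariate and outcome. With the pre-test covariate instead, the estimate stays between 0.461 and 0.477 in all twelve scenarios.

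**2. Residualised executive function in the mediation model**

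*Simple case by algebra.* All variables are standardised. Executive function E correlates 0.5 with mediator M and with parenting Y, is their only common cause, and M has no true effect on Y.

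- Unadjusted slope of M: 0.5 × 0.5 = 0.25.
- Adjusted for E: (0.25 − 0.5 × 0.5) / (1 − 0.25) = 0.
- Adjusted for E residualised on M: the residual is uncorrelated with M, so the slope stays at 0.25.
- Adjusted for E residualised on a neutral task N with corr(E, N) = 0.5: R = E − 0.5N, var(R) = 0.75, and cov(R, M) = cov(R, Y) = 0.5 − 0.5 × 0.25 = 0.375. The slope is (0.25 × 0.75 − 0.375²) / (0.75 − 0.375²) = 0.0469 / 0.6094 = 0.077. About 69% of the bias goes (0.173 / 0.25) and the rest remains.

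*Fuller case by simulation (n = 400,000).* Treatment acts on M (0.47) and directly on Y (0.20). E acts on M (0.5) and on Y (0.4). The true M-to-Y slope is 0.30. Treatment is in every model.

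| Executive-function term | Slope of M |
|---|---|
| none | 0.546 |
| full score | 0.300 |
| residual on M and treatment | 0.546 |
| residual on M only | 0.530 |
| residual on neutral task | 0.411 |
| residual on neutral task, if neutral inhibition is itself the confounder | 0.544 (0.544 with no term) |

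On the neutral-task reading, (0.546 − 0.411) / (0.546 − 0.300) = 55% of the bias is removed, or none if neutral inhibition is itself the confounder. With the residual on M only, the direct effect is recovered (0.199 against 0.20), but the mediator path is nearly untouched.

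In a variant with a baseline measure of M, the unadjusted slope is 0.575. Residualising E on baseline M gives 0.486, so 32% of the bias is removed (0.089 / 0.275). If baseline M is also in the model, the slope is 0.300, which is correct.

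**The case against.** The strongest reply is that the text never says that post-test values enter a model. It says only that the variables are measured twice and treated as confounders. The models section names no covariates, the pre-test precedes allocation, and covariate timing is often left to an analysis plan. This stands: a reader might infer that the treatment effect will be biased, but the documents support only that it can be. It does not dispose of the point, because the protocol does state the role of these variables and does so without excluding post-test values.

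A reader might also infer that the residualised score removes no confounding at all. The documents do not support that either. The sentence says only inhibitory control. The same section introduces the term as a component of executive function, and *Control variables* measures it with a separate neutral task, so the residual may be taken on that task. Some confounding is then removed, unless neutral inhibition is itself the confounder. Nor does the no-removal result carry over to attention and reflective functioning: for a mediator other than inhibitory control, analysed alone, the same algebra gives 0.077 rather than 0.25 even if the residual is taken on the child-emotion task.

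Residualising has an understandable motive, since executive function contains inhibitory control. But a pre-test score cannot be a consequence of treatment, so entering it whole does not remove treatment-induced change in the mediator.

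Finally, one might read parenting stress as a planned covariate because of where it is described. *Control variables* omits it, and *Aims and hypotheses* and *Fourth aim* make it an outcome. This is loose grouping in the Background and no more.

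**Conclusion.** The concern holds in a conditional form. The protocol does not confine adjustment to pre-test values, and post-test adjustment could shrink a true 0.47 to between 0.41 and 0.22 under the assumed g of 0.2 to 0.5 SD and r of 0.3 to 0.5. There is no bias if the intervention leaves the covariates unchanged or they are unrelated to outcome.

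The residualised score matters for the mediation aim, not for the randomised effect, where baseline adjustment serves precision. It removes none of the confounding of the inhibitory-control path if formed on the modelled mediator (next to none, 0.546 to 0.530, if treatment is in the model but not in the residualisation). It removes only part if formed on the neutral task, or on baseline inhibitory control that is not also modelled. The text leaves this open.

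Separately, *Maternal psychopathology* places the adjustment in the efficacy analysis, while *Control variables* places it in the cognitive-mechanism analyses. The two must be reconciled.

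**What to change.** 1. State that arm comparisons are adjusted only for pre-test psychopathology and pre-test executive function. Post-test values may be reported as outcomes.
2. In the mediation models, enter the pre-test executive-function score without residualising it. If a residual is kept as a sensitivity analysis, name the inhibitory-control score and time point that define it.
3. Say once which analyses carry which covariates, so that *Maternal psychopathology* and *Control variables* agree.
4. As a minor wording point, describe parenting stress only as the fourth-aim outcome and remove it from the group introduced as control variables.

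The cost is wording only. Both measures are already scheduled at pre-test, before allocation is known, so no data collection or sample-size change is needed.
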